### Interventions

All catgut embedding manipulations will be performed by an acupuncturist with national medical qualifications. The participants will receive treatment every 2 weeks for a total of 6 sessions.

### ACE Group

The selection of acupoints for treatment in the ACE group will be based on the theory that obesity is closely related to the spleen, stomach, and large intestine in traditional Chinese medicine and the Shu-Mu acupoints allocation method commonly used in the current clinical treatment of obesity. The acupoint prescription includes BL20 (Pishu), BL21 (Weishu), BL25 (Dachangshu), RN12 (Zhongwan), ST25 (Tianshu), and LR13 (Zhangmen). All acupoints except Zhongwan are selected bilaterally, for a total of 11 acupoints. The locations of these acupoints are shown in Table 2 and Figure 2.

**Table 2 table2:** The locations of acupoints.

Acupoints	Location
BL20 (Pishu)	In the upper back region, at the same level as the inferior border of the spinous process of the 11th thoracic vertebra (T11), 1.5 B-cun lateral to the posterior median line
BL21 (Weishu)	In the upper back region, at the same level as the inferior border of the spinous process of the 12th thoracic vertebra (T12), 1.5 B-cun lateral to the posterior median line
BL25 (Dachangshu)	In the lumbar region, at the same level as the inferior border of the spinous process of the fourth lumbar vertebra (L4), 1.5 B-cun lateral to the posterior median line
CV12 (Zhongwan)	On the upper abdomen, 4 B-cun superior to the center of the umbilicus, on the anterior median line
ST25 (Tianshu)	On the upper abdomen, 2 B-cun lateral to the center of the umbilicus
LR13 (Zhangmen)	On the lateral abdomen, inferior to the free extremity of the 11th rib

**Figure 2 figure2:**
[figure not shown]
Locations of acupoints and nonacupoints (NAs). Acupoints: BL20: Pishu, BL21: Weishu, BL25: Dachangshu, CV12: Zhongwan, LR13: Zhangmen, and ST25: Tianshu.

### Control Group

The acupoints in the control group will be selected based on the acupoints in the ACE group by moving each acupoint 2-3 cm outward horizontally in the median line (CV12 to the left side only) as a nonacupoints (not located on or overlapping with other meridians). They are labeled NA1, NA2, NA3, NA4, NA5, and NA6, respectively, for a total of 11 acupoints. The locations of these acupoints are shown in Table 3 and Figure 2, marked as red points.

**Table 3 table3:** The location of nonacupoints (NAs).

Nonacupoint	Location
NA1	The sitting position of the patient, in alignment with BL20 and the midpoint of the first and second lateral line of the bladder channel
NA2	The sitting position of the patient, in alignment with BL21 and the midpoint of the first and second lateral line of the bladder channel
NA3	The sitting position of the patient, in alignment with BL25 and the midpoint of the first and second lateral line of the bladder channel
NA4	The supine position of the patient, in alignment with RN12 and the midpoint of the left kidney and stomach channel
NA5	The supine position of the patient, in alignment with ST25 and the midpoint of the stomach and spleen channel
NA6	The sitting position of the patient, in alignment with LR13; a vertical line is made from Zhangmen to the spleen channel and the midpoint of the vertical line

### Operation Instruments

The thread-embedding needle used in this study is an 8# disposable needle (Jiangxi Glance Medical Equipment Co Ltd Production), and the medical protein string is an absorbable collagen line with the specification of 2-0, 2 cm × 20 length (Jiangxi Longteng Biotechnology Co, Ltd).

### Manipulation

The specific manipulation is as follows: participants are instructed to be placed in an appropriate position; the separate research assistant marks the acupoints or nonacupoints and routinely disinfects the skin around them; and a sterile sheet is spread, leaving only the buried area. Then, acupuncturists, who are unaware of the group allocation, take a sterile protein cord 1-2 cm long (the length depends on the location of the acupoints), place it on the front end of the trocar, connect the needle core, lift the partial skin with the thumb and forefinger of one hand, and pierce the needle with the other hand. When the piercing reaches the desired depth, apply appropriate push-and-twist techniques, push the needle core and remove the needle tube, and implant the sterile protein string in the subcutaneous tissue or muscle layer of the acupoints. After removing the needle, press the needle hole with a dry cotton ball for half a minute to stop the bleeding. Meanwhile, check that there is no thread residue exposure and no bleeding and then paste a bandage to protect the needle hole. It will be recommended that patients do not take a bath for 24 hours and keep the embedding place dry.

### Outcomes and Assessment

#### Primary Outcome

The primary outcome is the change of WC every 2 weeks, from baseline to end points. To collect the measurements, participants will stand their body upright, feet at shoulder width. An inelastic, 1-mm minimal tapeline will be used, set on the midpoint between the upper border hipbone and lower border 12th rib of the right midaxillary line. At the end of normal exhalation, they will be measured around the abdomen in the horizontal direction and without pressing the skin. The WC will be measured in millimeters (mm) and accurate to 1 mm.

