## Methods

### Study Design and Setting

This multicenter, double-blind, 16-week RCT will be conducted from August 2019 to September 2023 in 4 clinical centers: The Second Affiliated Hospital of Yunnan University of Chinese Medicine, The Sports Trauma Specialist Hospital of Yunnan Province, Kunming Hospital of Traditional Chinese Medicine, and ShengAi Hospital of Traditional Chinese Medicine. A total of 92 eligible participants with AO will be assigned to 1 of 2 groups (catgut embedding at acupoints or nonacupoints) using central randomization (1:1 allocation ratio). Every participant will receive a 12-week intervention period and a 4-week follow-up. The flowchart of this study is shown in Figure 1.

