### Sample Size Calculation

According to the existing literature [45], the mean BMI of simple obesity was 32.30 kg/m^2^, whereas after 12 weeks and 6 treatment of acupuncture combined with a low-energy diet, the mean BMI was 30.98 kg/m^2^, and the improvement value was 1.32 kg/m^2^. In contrast, the improvement value was 1.02 kg/m^2^ in a control group with a variation from 32.74 kg/m^2^ to 31.73 kg/m^2^ when treated by sham acupuncture combined with a low-energy diet, and the SD of the 2 groups was 0.31 kg/m^2^. In this project, the expected improvement value of the mean BMI of the Shu-Mu acupoints embedding group after treatment is 1.14 kg/m^2^ and that of the nonacupoints embedding group is 0.9 kg/m^2^, with the SD of each group being 0.31 kg/m^2^. The significant level is ɑ=.05, and the power of a test is 1 – β = 0.95. The sample size is 84 as calculated by German G*power software 3.1 [46]. According to the 10% dropout, the total sample is 92 cases, and 46 cases will be assigned to each group.

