### Statistical Analysis

All data will be analyzed by SPSS statistical software (version 19.0; IBM Corp). The clinical outcomes and baseline characteristics are based on the intention-to-treat population, which will include participants who have received at least one treatment. Continuous variables will be shown as the mean and SD, whereas the nonnormally distributed variables will be presented as the median and IQR. Categorical variables will be described as numbers and percentages. The normality of continuous variables will be determined using the Shapiro-Wilk test, Kolmogorov-Smirnov test, skewness, and kurtosis. The homogeneity of continuous variables will be determined by *F*-test, Brown-Forsythe, and Bartlett tests. Comparisons between groups will be made using independent samples 2-tailed *t* tests or nonparametric tests (Mann-Whitney *U* test). Repeated measures within groups (≥3) will be analyzed using one-way ANOVA or nonparametric (Friedman) tests. Paired 2-tailed *t* tests or nonparametric tests (Wilcoxon test) will be used for within-group pre-post comparisons. For categorical data, the chi-square test will be used to assess the significance of differences. Values of *P*<.05 will be considered significant using a 2-sided test.

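### The primary outcome is waist circumference change at every 2-week visit with no decisive visit named, so the trial has no single primary comparison and its 5% error rate is not secured

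*Protocol article*

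**What the plan says.** Under Primary Outcome, the article states: "The primary outcome is the change of WC every 2 weeks, from baseline to end points". The abstract says only that the primary outcome is waist circumference. Table 1 ticks WC at screening, at week 0 and at weeks 2, 4, 6, 8, 10, 12, 14 and 16.

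Study Design and Setting says how these weeks divide: "Every participant will receive a 12-week intervention period and a 4-week follow-up". The post-baseline visits therefore cover the intervention (weeks 2 to 12) and the follow-up (weeks 14 and 16).

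On testing, Statistical Analysis says:

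- Between groups: "Comparisons between groups will be made using independent samples 2-tailed *t* tests or nonparametric tests (Mann-Whitney *U* test").
- Over time: "Repeated measures within groups (≥3) will be analyzed using one-way ANOVA or nonparametric (Friedman) tests".
- Threshold: "Values of *P*<.05 will be considered significant using a 2-sided test".

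No section names week 12, week 16 or any other visit as the one on which the trial is judged.

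**The concern.** A primary outcome has to lead to one answer. Here the definition carries the whole visit schedule with it, and the only between-group methods named compare two groups on one value at a time. The methods for repeated measurements work inside each arm, so no longitudinal between-group test combines the eight visits into one result.

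The wording therefore leaves it open which visit decides the trial. Those conducting it could honestly report a positive primary result from whichever visit crosses P<.05. The visits also answer different questions: week 2 concerns an early response, week 12 the effect of the full course, and week 16 whether an effect persists after treatment stops. The nominal 5% error rate applies to one pre-specified comparison, and the article does not say which one that is.

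**Working it through.** **Inputs from the article**

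- Post-baseline WC visits: k = 8 (Table 1).
- Level: 0.05 two-sided for each test (Statistical Analysis; the sample-size section also gives alpha 0.05).
- Group size: 46 per arm randomised. The sample-size section's 84 before dropout is 42 per arm.

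**Assumptions that the article does not supply**

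- Success rule: at least one significant visit counts as primary success.
- Correlation r between the group-difference statistics at different visits: varied over a range.
- No true difference at any visit.

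**Step 1. The plan's own figure.** The article states a level of 0.05 and no error rate over visits. One pre-specified test at that level has a 5% false-positive chance, of which 2.5% favours acupoint embedding (ACE).

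**Step 2. Eight independent tests.** 1 − 0.95^8 = 0.337, or about 34%. Visits on the same people are positively correlated, so this is a reference ceiling rather than an expectation.

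**Step 3. Eight correlated tests.** The quantity is P(max |Z_j| > 1.96, j = 1 to 8), where the Z_j are standard normal with common correlation r. By simulation (400,000 draws):

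| r | Either direction | Favouring ACE |
|---|---|---|
| 0.5 | 25.1% | 12.5% |
| 0.7 | 19.2% | 9.6% |
| 0.9 | 12.0% | 6.0% |
| 0.95 | 9.5% | 4.8% |

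The last column is to be compared with 2.5%, not 5%.

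**Step 4. Other correlation patterns.** If the measured WC values follow an AR(1) series with adjacent-visit correlation 0.80 to 0.98, and each change is taken from the same baseline value, the two-sided result is 20.1% down to 17.8%. If the change behaves as a random walk, it is 17.7%. Both lie inside the 12% to 25% range.

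**Step 5. Actual t tests at the trial's size.** Simulated two-sample t tests gave 25.1% (42 per arm) and 25.7% (46 per arm) at r = 0.5, and 11.8% and 12.2% at r = 0.9. The normal approximation is adequate.

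**Step 6. Narrower reading: only weeks 12 and 16 are candidates.** For two tests the chance is 0.05 + 0.05 − P(both significant). This gives 9.1% at r = 0.5 and 7.0% at r = 0.9.

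**Step 7. After naming one comparison.** The rate returns to 5%. If all eight visits were kept as primary instead, a Bonferroni correction would require 0.05/8 = 0.00625 at each.

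**Step 8. Does the sample-size section settle the visit?** It does not. The 12-week duration there, "after 12 weeks and 6 treatment of acupuncture combined with a low-energy diet", describes the cited study. The trial's own expected improvements (1.14 versus 0.9 kg/m²) are placed only at some point following treatment, and they are for BMI, not WC.

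**The case against.** The strongest reply is that the article never says eight tests will be run, nor that any one of them decides the trial. The 2-week interval may be only the measurement frequency, because the secondary outcomes use nearly the same phrase in that sense. The plural end points may be stock wording, since it recurs for all five outcomes. On that reading the primary outcome is change from baseline to the end of the study, loosely expressed. A condensed article may also leave the visit-by-visit testing plan and any multiplicity adjustment to an analysis plan that is not shown.

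Much of this stands. A reader might infer that the trial has a false-positive rate of 12% to 25% as a matter of fact. The article does not support that: the range needs eight unadjusted tests, a rule that any significant visit is a success, and a correlation between 0.5 and 0.9, none of which is stated. It also counts significance in either direction. The absence of an adjustment method is not itself the defect.

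A reader might also infer that the trial was powered for a 12-week WC effect. It was not: the 12 weeks belong to the cited study, and the planning effect is in BMI.

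What the reply does not remove is the missing decisive visit. If the phrase is only a measurement schedule, the definition contains no time point at all, and both the end of intervention (week 12) and the end of follow-up (week 16) remain open. The time point is part of what the primary outcome is, and here the published definition spreads it over every visit. An analysis plan that named one visit would be narrowing that definition.

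**Conclusion.** The point holds as a defect in the definition: the primary outcome does not identify one between-group comparison, and the stated methods do not supply one. The size of the consequence is conditional. If any significant visit could be called primary success, the two-sided false-positive chance would be about 12% to 25% for correlations of 0.9 to 0.5, about 10% at 0.95 and about 34% under independence. Roughly half of each correlated-case figure would favour ACE, against a nominal 2.5%. If the choice lies only between weeks 12 and 16, the figure is about 7% to 9%. The correlation and the success rule are assumptions throughout. Every case considered exceeds 5%, so the direction of the problem does not depend on them once more than one visit may decide.

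**What to change.** Before unblinding, name one primary between-group comparison, tested at two-sided 0.05. The most natural choice is the difference in WC change from week 0 to week 12. Week 12 is the end of the intervention period given in Study Design and Setting, and it is consistent with the post-treatment improvement used in the sample-size section, although that calculation is for BMI and does not itself plan a WC effect. Week 16, or one overall longitudinal between-group contrast, would hold 5% equally well if the sponsor prefers that question; what matters is that one is fixed.

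Make all other visits, including week 16 if week 12 is chosen, secondary, and report them as between-group estimates with confidence intervals that do not decide the trial.

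This takes one sentence under Primary Outcome and one under Statistical Analysis, with no new data or visits. The downside is real: a significant difference at another visit can no longer count as primary success.

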#### Secondary Outcomes

The following secondary outcomes will be assessed:

The change of body weight (BW) will be measured every 2 weeks, from baseline to end points. Participants will be fasting 2 hours before the assessment. Shoes will be taken off, and only light clothing should be worn in a warm room while standing upright in the middle of the calibrated scale. BW will be measured in kilograms (kg) and accurate to 10 g.The change of BMI will be measured every 2 weeks, from baseline to end points: *BMI = BW (kg) ÷ height2 (m2)*. Height will be measured after the weight measurement, with the participants standing upright and close to the measuring stick. Height will be measured from the top of the head to the bottom of the feet in meters (m) and accurate to 1 mm.The change of hip circumference (HC) will be measured every 2 weeks, from baseline to end points. HC is the circumference of the most prominent point of the pelvis. Participants will stand upright, feet at shoulder width. The circumference at the end of the normal exhalation will be measured in millimeters (mm) and accurate to 1 mm.The visual analog scale (VAS) of appetite will be scored every 2 weeks, from baseline to end points. Appetite will be assessed by VAS as reported in Doucet et al [47] (see Figure 3): no appetite and minimal intake (score of 0), slight appetite and a small amount of intake (score of 1-3), moderate appetite and moderate intake (score of 4-6), and strong appetite and huge intake (7-10 score of 7-10).

All of the above measurements and evaluations will be performed by a separate researcher in the morning, with the patient coming to the hospital without eating breakfast.

**Figure 3 figure3:**
[figure not shown]
The visual analogue scale (VAS) of appetite.

#### Safety Evaluation

Due to puncture injury and protein wire stimulation, participants may experience local sterile inflammatory reactions such as redness, swelling, fever, pain, or small amounts of exudate within 1-5 days, which are normal, generally do not require treatment, and are kept under close observation. If there is more exudate from the acupoints; localized redness; swelling; increased pain; increased temperature; or even protein line spillage, wound fat liquefaction, or nerve damage, treatment will be suspended when these adverse reactions occur. Participants will be treated aggressively until they have fully recovered and reported to the study center for evaluation by a medical professional to see if the trial can continue. Serious or unexpected adverse events will be verbally reported within 24 to 48 hours. All information will be classified as a safety event.

#### Data Management and Quality Control

The outcome evaluator will complete the initial data in the case report form and enter it into a Microsoft Excel spreadsheet. The protocol will be reviewed several times by an acupuncturist with the title of director and a statistical expert. To ensure the smooth conduct of the study, the study leader shall provide uniform training to all study personnel before the start of the study and provide detailed operational training on the project implementation protocol and observation indicators to familiarize them with the study process and specific implementation details to ensure the reliability of the study results. The project leader shall supervise and check the entire study process to confirm that all study data and case report forms are recorded and reported truthfully, accurately, completely, and consistently with the original data. Any deviation from the protocol will be reported to the ethics committee of The Sports Trauma Specialist Hospital of Yunnan Province, which will ultimately decide whether we must change the protocol or terminate the trial. To ensure participant compliance, all treatments and tests will be provided free of charge.

### Statistical Analysis

All data will be analyzed by SPSS statistical software (version 19.0; IBM Corp). The clinical outcomes and baseline characteristics are based on the intention-to-treat population, which will include participants who have received at least one treatment. Continuous variables will be shown as the mean and SD, whereas the nonnormally distributed variables will be presented as the median and IQR. Categorical variables will be described as numbers and percentages. The normality of continuous variables will be determined using the Shapiro-Wilk test, Kolmogorov-Smirnov test, skewness, and kurtosis. The homogeneity of continuous variables will be determined by *F*-test, Brown-Forsythe, and Bartlett tests. Comparisons between groups will be made using independent samples 2-tailed *t* tests or nonparametric tests (Mann-Whitney *U* test). Repeated measures within groups (≥3) will be analyzed using one-way ANOVA or nonparametric (Friedman) tests. Paired 2-tailed *t* tests or nonparametric tests (Wilcoxon test) will be used for within-group pre-post comparisons. For categorical data, the chi-square test will be used to assess the significance of differences. Values of *P*<.05 will be considered significant using a 2-sided test.

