**Methods:**

This is a multicenter, double-blind, 16-week randomized controlled trial. A total of 92 eligible participants with AO will be randomly divided into 2 groups (1:1 allocation ratio). The ACE group will receive catgut embedding at acupoints and the control group will receive catgut embedding at nonacupoints. The intervention will be performed every 2 weeks for a total of 6 sessions. Follow-up will be performed every 2 weeks for a total of 2 visits. The primary outcome is waist circumference. Secondary outcomes include body weight, BMI, hip circumference, and the visual analog scale of appetite. Upon the completion of the trial, we will evaluate the effect of catgut embedding at acupoints or nonacupoints on obesity indicators in patients with AO. For treatment outcomes, an intention-to-treat analysis will be performed.

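### As stated, the between-arm tests of WC change use observed values only, so each visit is an available-case comparison rather than the intention-to-treat analysis the article names

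*Protocol article*

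**What the plan says.** The Primary Outcome section defines the endpoint: "The primary outcome is the change of WC every 2 weeks, from baseline to end points". Table 1 schedules WC at screening, at week 0, and at eight later visits from week 2 to week 16. The Study Design and Setting section says: "Every participant will receive a 12-week intervention period and a 4-week follow-up".

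The abstract states: "For treatment outcomes, an intention-to-treat analysis will be performed". The Statistical Analysis section repeats the label and bases outcomes on the "intention-to-treat population, which will include participants who have received at least one treatment".

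That section names one between-arm approach for continuous outcomes: "Comparisons between groups will be made using independent samples 2-tailed *t* tests or nonparametric tests (Mann-Whitney *U* test"). The repeated-measures methods it lists, one-way ANOVA and the Friedman test, are for comparisons within a group.

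The Sample Size Calculation expects losses: "According to the 10% dropout, the total sample is 92 cases, and 46 cases will be assigned to each group". The Blinding and Informed Consent section allows withdrawal at any time without a reason. The article does not say how a participant with no WC value at a visit enters the comparison. It neither imputes such a participant nor states that they are left out.

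**The concern.** A change score exists only for a person measured at the later visit. A two-sample t test or rank test on that score takes one number per person and ignores whoever has none. Unless a rule supplies the missing value, members of the intention-to-treat set who have left do not count at the visits they miss. Their earlier WC measurements carry no information into those later comparisons.

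This matters if those who leave differ from those who stay and the arms lose such people unequally. Participants who see no reduction are plausible leavers. The arm that loses more of them then looks better than it should, and the between-arm WC difference moves with the loss pattern while the report calls it intention-to-treat.

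**Working it through.** **Size of the expected loss.** The plan's figure is 84 raised to 92 for 10% dropout. 84 × 1.10 = 92.4, which matches 92; dividing instead gives 84 / 0.90 = 93.3. The expected loss is therefore 92 − 84 = 8 on the plan's step, or 92 × 0.10 = 9.2. How the 84 itself was obtained is a separate matter and plays no part here.

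**Power.** The article gives no effect or SD for WC, so only its BMI inputs can be used: difference 1.14 − 0.90 = 0.24, SD 0.31, ratio 0.24 / 0.31 = 0.77. With a two-sided t test at 0.05, power is 0.957 with 46 per arm. It is 0.934 with 41 per arm (92 × 0.9 = 82.8). The loss of power is small.

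**Bias of an observed-values contrast.** In one arm let a fraction p leave, and let leavers improve by δ less than stayers.
- Mean for everyone = stayers' mean − pδ, so the observed mean overstates improvement by pδ.
- Shift in the arm difference (ACE minus control) = (p_ACE − p_control) × δ.
- Standard error in SD units = √(1/n₁ + 1/n₂), with n = 46 × (1 − p).

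The dropout splits and δ are assumptions, because the article gives neither. δ is in units of the SD of WC change.

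| Dropout, two arms | n per arm | SE | Shift, δ = 0.5 | Shift, δ = 1.0 | Shift / SE |
|---|---|---|---|---|---|
| 10% / 10% | 41.4 / 41.4 | 0.22 | 0 | 0 | 0 |
| 15% / 5% | 39.1 / 43.7 | 0.22 | 0.05 | 0.10 | 0.23 to 0.45 |
| 18% / 2% | 37.7 / 45.1 | 0.22 | 0.08 | 0.16 | 0.36 to 0.73 |

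The shift favours whichever arm loses more, so its sign is unknown in advance.

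**An extreme case on the BMI figures.** Suppose stayers show the planned 1.14 and 0.90, and leavers show no change. The difference for everyone is then:
- 10% / 10%: 0.90 × 1.14 − 0.90 × 0.90 = 0.216
- 15% ACE / 5% control: 0.85 × 1.14 − 0.95 × 0.90 = 0.114
- 5% ACE / 15% control: 0.95 × 1.14 − 0.85 × 0.90 = 0.318

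An observed-values test would report 0.24 in all three. This is harsher than the table and concerns BMI; it shows only that direction and size depend on who leaves.

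**What the earlier visits can recover.** A simulation used 46 per arm, eight visits, autoregressive correlation 0.8 to 0.95 and a true final difference of 0.774 SD, with dropout of 7% to 13% per arm depending on the last recorded change. The observed-values contrast was off by 0.01 to 0.08 SD. A likelihood estimate using all earlier visits was off by less than 0.01 SD, with essentially the same standard error. Dropout that depends on recorded values is the setting in which a likelihood method is expected to do well, so this supports the fix only under that mechanism.

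**The case against.** The strongest reply is that naming a test does not fix how missing values are handled. A t test can follow multiple imputation, and an imputation rule commonly sits in a full protocol or SAP, neither of which is shown. That stands: the absence of a rule is not by itself a fault in a condensed article. What remains is that the stated between-arm method does not deliver the named analysis unaided, and a better method is available from data already collected.

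The second reply is that the effect is small. Both arms receive the same procedure and participants are to be blinded, which makes very unequal dropout less likely. Even the most unequal split in the table shifts the result by less than one standard error. This also stands, and it limits the weight of the point.

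A reader might infer more than the article supports:
- **That the primary comparison becomes a completers' analysis and recorded values are discarded.** Someone who leaves at week 8 still counts through week 8. The earlier values are used at their own visits but not for the later contrast.
- **That suspended treatment means a missing WC.** The Safety Evaluation section says "treatment will be suspended when these adverse reactions occur". It does not say that measurement stops.
- **That inflating to 92 shows leavers will be excluded.** Such inflation is routine and compatible with any missing-data method.
- **That 10% dropout crosses a limit.** The article sets none.
- **That case-wise losses in the Friedman test harm the arm comparison.** That test is assigned to within-group use only.

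**Conclusion.** The point holds as an available-case concern. The article names intention-to-treat, expects about 8 to 9 of 92 to drop out, and states between-arm tests that use observed values only unless a rule is added. The consequence is possible bias in the later WC contrasts, near weeks 12 to 16, and little loss of power. Its size is zero under equal, similar dropout. It is about 0.05 to 0.16 SD (0.2 to 0.7 standard errors) under the assumed splits of 15% vs 5% to 18% vs 2% with δ of 0.5 to 1.0 SD. It cannot be expressed in millimetres because no SD for WC change is given. This is a worthwhile, inexpensive improvement, not evidence that the trial's result will be wrong.

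**What to change.** In the Statistical Analysis section, make the between-arm WC analysis a likelihood-based mixed model for repeated measures on all recorded WC changes at weeks 2 to 16. Include arm, visit, arm-by-visit and baseline WC, with an unstructured within-person covariance. With eight visits that is 8 × 9 / 2 = 36 covariance parameters from 92 participants, so state in advance a simpler structure to use if the model does not converge.

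Name in advance the one visit whose arm difference is primary. The present definition covers every two-weekly visit, and the model needs a single contrast to report.

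Add one delta-adjusted sensitivity analysis that worsens the unobserved WC changes, for example by 0.5 and 1.0 SD, reported beside the main result. This covers leavers who do worse than their recorded values predict.

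If the t test or Mann-Whitney test is kept without a missing-value rule, describe it as an available-case analysis and not as intention-to-treat.

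The cost is wording, a slightly less simple primary analysis and one extra table. The two-weekly WC values are already scheduled, and the stated software fits mixed models.
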